**Table 1 Tab1:** **Definitions of behaviour taxonomy** [51] **and application to intervention**

**Behaviour change technique number and label**	**Definition of BCT**	**Materials**	**Summary (use of technique in intervention)**
***Social support***			
1. Social support (unspecified)	Advise on, arrange or provide social support or non-contingent praise or reward for the behaviour.	Intervention booklet	Participants received intervention booklets outlining the benefits of walking during treatment, advising them to increase levels of walking and encouraging them to walk with friends and family.
***Feedback and monitoring***			
11. Self-monitoring behaviour	Establish a method for the person to monitor and record the behaviour as part of a behaviour change strategy.	Pedometer, intervention booklet & walking diary	Patients were asked to keep a daily record of the number of steps taken alongside the intensity and duration of their walking
***Repetition and substitution***			
29. Graded tasks	Set easy-to-perform tasks, making them increasingly difficult, but achievable, until behaviour is performed.	Intervention booklet & walking diary	Patients were encouraged to set weekly goals and to gradually increase the number of steps taken week by week. They were asked to challenge themselves with each week but also set realistic/achievable goals whilst taking their chemotherapy schedules into consideration.
***Goals and planning***			
61. Goal setting (behaviour)	Set or agree to set a goal defined in terms of the behaviour to be achieved.	Walking diary	Patients were asked to set specific weekly step count goals stating when and how many steps they intend to take
65. Action planning	Prompt detailed planning of performance of the behaviour (must include at least one of context, frequency, duration and intensity). Context may be environmental (physical or social) or internal (physical, emotional or cognitive).	Walking diary	Patients were encouraged to set weekly plans outlining the amount of walking they intend to do each day of the week. Action plans included the duration, intensity, day of the week and time of day they aim to complete their walking.
***Comparison of outcomes***			
72. Persuasive source	Present verbal or visual communication from a credible source in favour of or against the behaviour.	Intervention booklet & verbally	Each patient was presented with an intervention booklet stating the benefits of walking which were adapted from credible sources. The patients’ consultant also verbally recommended and encouraged patients to participate in the physical activity involved in the study.

### Procedure

The researcher will recruit participants, collect cognitive and psychosocial data at pre and post-intervention and facilitate the delivery of the physical activity intervention. Initially, consenting participants will be asked by the researcher to complete a self-report cognitive functioning questionnaire, a battery of objective tests of cognitive impairment and a questionnaire pack assessing quality of life and emotional well-being pre-chemotherapy to allow familiarisation with the researcher and research materials. They will be asked to wear ActiGraph GT3X+ accelerometers for 10 hours a day for 7 days for a measure of habitual walking after the familiarisation assessment [63]. These data will be collected prior to receiving chemotherapy.

After completing two cycles of chemotherapy, participants will be asked to complete the same measures again at the clinic. Patients will then be randomised to either the intervention or control group following the procedures outlined above. The walking intervention starts after 2 cycles of treatment in line with recommendations from oncologists who suggests that the intervention will be better received by patients after they have had 2 cycles of chemotherapy and understand what they are facing with regard to treatment side effects. The intervention group will be asked to commit to the 12 week walking intervention and will be provided with a booklet outlining the amount of walking they should take part in alongside guidance and tips on how to incorporate this into their daily routines. The intervention group will also be asked to commit to a minimum of 150 minutes of moderate intensity walking per week for the duration of the 12 week intervention, in line with recommended guidelines [61]. They will be told how to monitor their own intensity levels and will be encouraged to aim to walk at moderate levels of intensity for 150 minutes a week for the duration of the intervention. Walking schedules will be self-prescribed by participants but the researcher will recommend that they begin by completing 10 minutes of walking at any one time and then steadily increase the duration of walking to 30 minutes. Participants will be provided with a pedometer for the duration of the intervention and will be asked to log their walking for the 12 week period. Those randomised to the control group will continue to receive usual care alone.

Post-intervention (after the completion of 6 cycles of chemotherapy), all participants will be asked to wear the accelerometer for a further 10 hours a day for 7 days. In addition, they will be asked to complete the same questionnaires and neuropsychological tests as those completed at pre-chemotherapy and mid way through chemotherapy. At the end of the study the control group will receive the intervention booklet (see Figure 1 for flow chart of study methods).

**Figure 1 Fig1:**
[figure not shown]
Flow diagram illustrating study methods.

### Measures of physical activity

Accelerometers (motion sensors which detect accelerations produced by the human body), will be worn by all participants for 10 hours a day for 7 days at baseline and post-intervention to assess habitual physical activity [63]. Pedometers will be worn by participants randomised to the intervention group for 10 hours a day for the duration of the twelve week intervention in order to record frequency of steps taken. They will also complete the Borg Rating of Perceived Exertion Scale [64] and The Talk Test [65] to subjectively monitor the intensity of their walking during the intervention.

### Outcome measures

All outcome measures will be completed at three time points: baseline (familiarisation), mid way through chemotherapy (pre-intervention) and after the completion of chemotherapy (post-intervention). All outcome measures have been validated in this population.

### Objective measures of cognitive functioning

The Stroop test [66] will be used to measure executive function. Working memory will be tested using forwards and backwards digit span as used in the Wechsler Adult Intelligence Scale-III [67]. Sustained attention will be measured using a computerised version of the Sustained Attention to Response Task [68]. Visuospatial skills will be measured using the WAIS Block Design subset as used in the Wechsler Adult Intelligence Scale-III [67].

### Subjective measure of cognitive functioning

The Cognitive Failures Questionnaire [69] is a 25 item questionnaire which will be used to assess the primary outcome measure of perceived cognitive function. The questionnaire will ask participants to reflect on minor mistakes made across a one month time frame. Responses are measured on a five-point Likert scale ranging from ‘very often’ to ‘never’.

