**Method:**

This study will deliver a home-based moderate intensity walking intervention to women diagnosed with breast cancer mid-way through their chemotherapy treatment and will compare them to patients receiving usual care alone. The primary outcome measure for this intervention is changes in an objective measure of memory assessed using the Digit Span. Secondary outcome measures include: objective measures of executive function; attention; visual spatial skills; self report cognitive function; self-report fatigue; anxiety; depression; mood and self-esteem. As emotional distress has been associated with self-reporting of cognitive problems, this intervention will further test whether emotional distress mediates between the amount of walking undertaken during the intervention period and levels of self-reported cognitive functioning.

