## Methods

### Objectives/hypothesis

The primary aim of the study is to investigate the effectiveness of a home-based moderate intensity walking intervention on reducing cognitive impairment of breast cancer patients receiving chemotherapy. Our primary hypothesis is that women who complete the physical activity intervention will demonstrate less impairment in memory in comparison to women in the non-intervention group. Our secondary hypotheses are that the intervention group will perform better than the control group on objective and subjective measures of cognitive function, and will report better quality of life outcomes than the control group. Furthermore, within the intervention group, emotional well-being will mediate between physical activity level and level of subjectively reported and objectively tested impairment in memory, attention and concentration.

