### Sample size

Sample size for the study was calculated based upon previously published data [37,38] and Cohen’s Power Primer [74]. According to a prospective calculation, for a repeated measures ANOVA, 26 participants per group are required to detect a large effect size with power of 0.80 and α set at .05. It is reasonable to assume a large effect size in this population based upon previous research [37,38] and their memory performance on the digit span. Allowing for 20% attrition due to withdrawal and illness we aim to recruit 31 patients per group.

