### Statistical analyses

Quantitative data will be entered into Statistical Package for the Social Sciences (SPSS) and intention to treat analysis will be used in line with the CONSORT statement. To test the effectiveness of the physical activity intervention on cognitive function, a series 2x2 mixed ANCOVAs will be carried out controlling for age and menopausal status (controlling for natural differences in cognitive function associated with age and menopausal status). Participant group (intervention or control) will be entered as the between subjects factor and time (pre-intervention and post-intervention) will be entered as the within subjects factor. In addition, to test the effectiveness of the intervention on quality of life and measures of well-being another series of 2x2 mixed measures ANOVA will be carried out between the intervention group and control group. Post-hoc analysis will be carried out using a series of t-tests to check for differences between the intervention and control group. Lastly, to test whether emotional distress mediates between amount of physical activity (duration of walking and steps taken) and self-report cognitive functioning for the intervention group, a series of mediation analyses will be carried out using regression analyses.

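### The Cognitive Failures Questionnaire is labelled the primary outcome in the Methods, contradicting the abstract, which makes change in Digit Span primary and self-reported cognition secondary

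*Protocol article*

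**What the plan says.** The protocol article describes the primary outcome in several places, and they do not agree.

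- **Abstract, Method:** "The primary outcome measure for this intervention is changes in an objective measure of memory assessed using the Digit Span". The same paragraph continues: "Secondary outcome measures include: objective measures of executive function; attention; visual spatial skills; self report cognitive function". Digit Span is therefore primary and self-report secondary.
- **Objectives/hypothesis:** "Our primary hypothesis is that women who complete the physical activity intervention will demonstrate less impairment in memory". No instrument is named. Subjective cognition comes under the secondary hypotheses, where "the intervention group will perform better than the control group on objective and subjective measures of cognitive function".
- **Objective measures of cognitive functioning:** "Working memory will be tested using forwards and backwards digit span". Digit Span is not called primary here.
- **Subjective measure of cognitive functioning:** the Cognitive Failures Questionnaire is the instrument "which will be used to assess the primary outcome measure of perceived cognitive function".
- **Sample size:** "26 participants per group are required to detect a large effect size with power of 0.80 and α set at .05". The large effect is justified partly by performance on the digit span.
- **Statistical analyses:** for cognitive function, "a series 2x2 mixed ANCOVAs will be carried out controlling for age and menopausal status", with group as the between-subjects factor and time (pre- and post-intervention) as the within-subjects factor. No test is identified as primary.

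**The concern.** One measure cannot be both a secondary outcome and the primary outcome. A reader who works only from the Methods finds the questionnaire labelled primary; a reader of the abstract finds Digit Span. The analysis section does not decide between them.

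Two features of this trial make the conflict more than cosmetic. First, the Background reports that subjective and objective measures of cognitive decline are not associated with each other. On the authors' own account, the two candidates address different questions and may give different answers. Second, the Randomisation section says that neither participants nor the research team are masked. The questionnaire is rated by women who know their allocation, so expectation can act on it directly.

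At stake are which result counts as the trial's main finding, and whether the alpha of 0.05 in the sample-size section describes the error rate of that finding.

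**Working it through.** **1. Where each part of the article points**

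| Section | Digit Span / memory | Self-reported cognition |
|---|---|---|
| Abstract, Method | primary | secondary |
| Objectives/hypothesis | primary hypothesis (memory) | secondary hypothesis |
| Objective measures | described, no rank | – |
| Subjective measure | – | primary |
| Sample size | basis of the calculation | not mentioned |
| Statistical analyses | no rank | no rank |

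Three sections favour Digit Span and one contradicts them. The contradicting section is the only one in the Methods that attaches the primary-outcome label to a measure.

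**2. Reproducing the plan's own figure**

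Inputs from the Sample size section: alpha 0.05, power 0.80, a large effect. Assumptions: large means d = 0.8, and the test is two-sided; the article states neither. With two groups and two time points, and leaving the covariates aside, the group-by-time test is a two-sample t-test on change scores, so d is read on that scale.

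- Normal approximation: n = 2(1.960 + 0.842)² / 0.8² = 24.5, so 25 per group.
- Exact t-test: n = 25.5, so 26 per group. Power at 26 is 0.807.

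The stated 26 is reproduced for one test at 0.05.

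**3. Error rate if either measure could be reported as primary, each tested at 0.05**

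- Independent tests: 1 − 0.95² = 0.0975, or 9.75%.
- Correlated tests: 1 − P(|Z₁| < 1.96 and |Z₂| < 1.96), with Z₁ and Z₂ bivariate normal. The correlations below are assumed.

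| Correlation | Chance of at least one false positive |
|---|---|
| 0 | 9.75% |
| 0.1 | 9.7% |
| 0.3 | 9.5% |
| 0.5 | 9.1% |
| 0.7 | 8.3% |

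The Background's statement of no association puts this pair near the top of the table. Counting only false positives that favour the intervention, the independent case gives 1 − 0.975² = 4.9%, against 2.5% for one test.

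**4. If both were meant as primary**

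With alpha split equally, 0.025 each, and d = 0.8:

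- Power with 26 per group is about 0.72 for each outcome.
- For power of 0.80, the exact t-test needs 31 evaluable per group (30.99 before rounding).
- With 20% attrition, 31 / (1 − 0.20) = 38.75, so 39 recruited per group.

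The plan recruits 31 per group in total, which would leave no allowance for loss. The stated sample size therefore fits a single primary outcome.

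**The case against.** The best defence is that the primary outcome is already identifiable. The abstract names Digit Span outright, the primary hypothesis concerns memory, and the sample size rests on digit span. Against these stands one phrase, which may be a slip. This is largely right, and it is why the repair is simple. It does not remove the conflict, because the label sits in the Methods and nothing there overrides it.

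A second defence is that a journal article may leave the ranking of tests, a multiplicity rule and Digit Span scoring to the full protocol or analysis plan. That is fair, and none of those is counted here as a defect in itself. The analysis section matters only because it does not resolve a contradiction that the article itself contains.

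A third is that Digit Span is not protected from bias either. The Procedure section has the researcher both collect the cognitive data and facilitate the intervention, and the research team is unmasked. This stands: lack of masking affects both candidates, by different routes.

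A reader might go further and infer that the trial plans to claim success on whichever measure is positive, or that every ANCOVA has equal standing at 0.05. The documents support neither. No sentence says that either measure suffices, and the analysis section gives neither an alpha nor an order of importance; the 0.05 appears only in the sample-size calculation. Nor is it sound to compute an error rate over all the outcomes as though each were a candidate primary. Only two measures are given that label anywhere, and the Background's statement of no association covers only the objective–subjective pair.

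**Conclusion.** The contradiction is real and concerns the outcome on which the trial's conclusion rests, so it must be settled before results are known. The weight of the document favours Digit Span.

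The size is conditional. If the ambiguity let either measure be reported as primary at 0.05, the chance of at least one false positive would be 9.75% under independence and about 8.3% at an assumed correlation of 0.7, against the intended 5%. This describes what the wording leaves open, not a procedure that the plan states. It rests on two candidates, two-sided tests and no adjustment. The sample-size check also rests on reading a large effect as d = 0.8.

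**What to change.** 1. In the section on the subjective measure, call the Cognitive Failures Questionnaire a secondary outcome.
2. In the section on objective measures, name Digit Span as the sole primary outcome and state in advance which one score is used (forwards, backwards or total).
3. In Statistical analyses, name the primary test: the between-group difference in pre- to post-intervention change in that score, at 0.05. This is the group-by-time contrast in the model already planned, and it matches the abstract's definition of the outcome as change.
4. State that all other outcomes are secondary and cannot support the primary claim.

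The cost is wording in three sections. No extra patients, data or visits are needed, and the 26 per group needs no change on this account. If the investigators do intend two primary outcomes, they should say so, state a multiplicity rule and redo the sample size.

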### Subjective measures of emotional wellbeing

Anxiety and depression will be measured using the 14 items Hospital Anxiety and Depression Scale [70]. Fatigue will be measured using The Functional Assessment of Cancer therapy-Fatigue [71]. Self esteem will be measured using the Self-Esteem Scale [72]. The rating scale requires participants to indicate how they feel in relation to a series of 10 statements. Emotional Distress will be measured using the shortened version of Profile of Mood States [73]. Participants will first be asked to complete questions regarding their anxiety and depression, followed by self-esteem, fatigue, perceived cognitive function and lastly mood.

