### Design

The study is a randomised controlled trial comparing the home based walking intervention group with care as usual control group. Outcomes will be assessed at two time points: mid-way through chemotherapy (pre-intervention) and after the completion of chemotherapy (post-intervention). All participants will also complete outcome measures prior to receiving chemotherapy to familiarise them with study materials, study setting and the researcher.

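### Distress and self-reported cognition share a single post-randomisation assessment, so the planned regressions can show that they are associated but not that distress mediates the effect of walking

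*Protocol article*

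**What the plan says.** The relevant statements are spread over several sections of the Protocol article.

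- **Schedule.** Under Outcome measures, every outcome is collected three times: before chemotherapy for familiarisation, mid-way through chemotherapy, and after it ends. Under Procedure, the mid-way assessment comes first and then "Patients will then be randomised to either the intervention or control group following the procedures outlined above". The only later assessment follows six cycles: "In addition, they will be asked to complete the same questionnaires and neuropsychological tests as those completed at pre-chemotherapy and mid way through chemotherapy".
- **Mediator.** Under Subjective measures of emotional wellbeing: "Emotional Distress will be measured using the shortened version of Profile of Mood States". That section also fixes the order of the pack. Anxiety and depression come first, "followed by self-esteem, fatigue, perceived cognitive function and lastly mood".
- **Outcome.** Under Subjective measure of cognitive functioning, the Cognitive Failures Questionnaire asks women to "reflect on minor mistakes made across a one month time frame".
- **Analysis.** Under Statistical analyses, regressions are planned "to test whether emotional distress mediates between amount of physical activity (duration of walking and steps taken) and self-report cognitive functioning", within the intervention group. The Abstract (Method) states the same aim. Objectives/hypothesis predicts that emotional well-being will mediate, and extends this to objectively tested cognition.

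No measurement of distress or cognition is described during the 12 weeks of walking.

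**The concern.** A mediation claim needs an order: walking changes distress, and distress then changes cognition. Here the two later links of that chain are observed once each after randomisation, together. The two earlier distress scores precede the walking, so they can serve as baseline adjustment but not as the mediator.

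The reverse order is plausible on the article's own account. The Discussion describes cognitive difficulties hampering return to work and thereby lowering self-esteem, which runs from cognition to emotional state. The Background suggests that poorer psychosocial well-being may predispose to impairment, which runs the other way.

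At stake is what the trial may conclude. If noticing cognitive failures is what upsets women, the planned regressions will tend to return an indirect effect through distress all the same. No detail in an analysis plan can supply a time order that was not collected.

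**Working it through.** **The plan's own figure.** The plan gives no figure for the mediation analysis. Its only design figure is 26 per group under Sample size. Taking a large effect as d = 0.8 and a two-sided 5% test (both assumed, since the text says only that the effect is large), the exact two-sample t-test needs 25.5, so 26, with power 0.807. The figure is reproduced, but it concerns a comparison of groups. It is used below only as the size of the intervention arm, with 31 as the recruited number.

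**Schedule laid out.**

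| Occasion | Relative to randomisation | Distress | Self-reported cognition |
|---|---|---|---|
| Pre-chemotherapy | before | yes | yes |
| Mid-chemotherapy | before | yes | yes |
| During the 12 weeks | after | none described | none described |
| After six cycles | after | yes | yes |

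There is one post-randomisation occasion for each, and it is the same one. The planned lag between mediator and outcome is zero.

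**What the regressions return when the order is reversed.** Let X be walking, Y cognition and M distress, all standardised, with signs set so that effects are positive. Suppose X affects Y with path c, Y affects M with path d, and M has no effect on Y. Then:

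- a (M on X) = c × d
- b (M in the regression of Y on X and M) = (d − c × cd) / (1 − (cd)²)
- indirect effect = a × b; share of the total effect = a × b / c

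With c = 0.4 and d = 0.5: a = 0.20; b = (0.5 − 0.08) / 0.96 = 0.4375; indirect = 0.0875; share = 0.0875 / 0.4 = 21.9%. The true share is 0%.

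Over the grid, using share = d²(1 − c²) / (1 − c²d²), which is the same formula simplified:

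| | d = 0.4 | d = 0.5 | d = 0.6 |
|---|---|---|---|
| c = 0.3 | 14.8% | 23.3% | 33.9% |
| c = 0.4 | 13.8% | 21.9% | 32.1% |
| c = 0.5 | 12.5% | 20.0% | 29.7% |

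The range is 12.5% to 33.9%. All path values are assumed; the documents give none.

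**How often this would be declared significant.** The same reversed chain was simulated, and mediation was called when both a and b had p < 0.05.

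| c / d | n = 26 | n = 31 | n = 2000 |
|---|---|---|---|
| 0.3 / 0.3 | 2% | 2.5% | 99% |
| 0.3 / 0.5 | 7% | 9% | 100% |
| 0.5 / 0.5 | 14% | 18% | 100% |
| 0.5 / 0.7 | 40% | 49% | 100% |

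The first and last rows lie outside the grid above. The small arm hides the bias, and a larger one would expose it as a firm false finding.

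**Would a mid-way distress score alone help?** Keep c = 0.4 and d = 0.5 for mid-way cognition and mid-way distress, and let mid-way cognition carry to final cognition with path 0.7, with no further effect of walking. Then r(X,M) = 0.20, r(X,Y) = 0.4 × 0.7 = 0.28 and r(M,Y) = 0.5 × 0.7 = 0.35. So b = (0.35 − 0.28 × 0.20) / 0.96 = 0.306, the indirect effect is 0.061, and the share is 0.061 / 0.28 = 22%, as before. The 0.7 cancels, so any persistence gives the same share. If mid-way cognition is also measured and adjusted for, b becomes zero in this chain, because mid-way distress is related to final cognition only through mid-way cognition (0.35 = 0.5 × 0.7).

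**The case against.** The strongest reply is about size and rank. This is the last-listed secondary analysis. It leaves the randomised comparison, the primary outcome and the sample size alone. Walking is logged throughout the 12 weeks, so the exposure largely precedes both other variables. With 26 to 31 women a false mediation result would usually miss significance. All of that stands. It limits the consequence but does not make the planned conclusion one that the schedule can support.

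Several stronger readings are tempting and are not supported.

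- A reader might infer from the pack order that the mediator is recorded after the period the outcome describes. The article gives no recall window for the POMS, so the two periods may overlap. The anxiety and depression scale precedes the cognition questionnaire, and the hypothesis speaks of emotional well-being more broadly. Moving mood ahead of cognition would only exchange one possible order effect for another.
- A reader might infer that neither construct is measured before randomisation. Both are, twice.
- A reader might say that both are collected at one visit. Recruitment has questionnaires completed at home and posted, while Procedure places the mid-chemotherapy measures at the clinic. Only a shared assessment occasion is established.
- A reader might conclude that the trial will report false mediation. A biased estimate is not the same as a declared finding, and the simulated rates at n = 26 and 31 do not bear that out.

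**Conclusion.** The point holds as a limit on interpretation. Distress and self-reported cognition have one post-randomisation measurement each, on one occasion, so the planned regressions cannot tell walking, distress, cognition from walking, cognition, distress. If the second order were the whole truth, about 12% to 34% of the total effect would be credited to distress under assumed paths of 0.3 to 0.5 and 0.4 to 0.6. These figures are illustrative: they rest on linear standardised relations, no measurement error and no baseline adjustment. Adjusting for pre-intervention scores is worthwhile but does not settle direction. More participants would sharpen the biased estimate and not correct it. The primary result is not affected.

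**What to change.** In the Abstract (Method), Objectives/hypothesis and Statistical analyses, describe this secondary analysis as a concurrent association between walking, distress and self-reported cognition, adjusted for the pre-intervention distress and cognition scores already collected. Fit the reverse model, with cognition as the intermediate and distress as the outcome, and report the two side by side. Do not conclude mediation from either. The cost is a change of wording and one further regression.

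If a time-ordered test is wanted, post both the POMS and the Cognitive Failures Questionnaire about half-way through the 12 weeks, using the pre-paid return already described under Recruitment. Relate mid-way distress to final cognition with adjustment for mid-way cognition. Posting distress scales alone leaves the same bias, as shown above. The cost is one short mailing and slight extra questionnaire burden during chemotherapy. Other confounding of distress and cognition would remain. The order of questionnaires in the pack need not change.
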